**Analysis:**

Analysis will be by intention to treat. Intra-cluster (practice) correlation coefficients will be determined and published for all primary outcome variables to assist future research. The effect of the intervention on outcomes measured on a continuous scale will be estimated and tested using mixed model analysis of variance in which time and treatment group will be fixed effects and GP practice and subject nested within practice will be random effects. The effect of the intervention on the dichotomous variables (such as smoking status, patient knowledge) will be analysed using generalised estimating equations with a logistic link and a model structure that is analogous to that described above.

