#### Outcome evaluation

Quantitative outcomes were measured using instruments with demonstrated validity and reliability. A portable carbon monoxide (CO) analyser was used to validate participants' self-report of smoking status. These measures were implemented by two members of the research team who were blinded to the patients' group allocation. Data collectors received training in spirometry and use of the CO analyser.

Outcomes were measured at three points in time – at recruitment (baseline), 6 months and at 12 months after randomisation. [Table 1 shows outcomes measures being collected] These were measured at the participant's residence or at the GP practices as preferred by the patient.

**Table 1 T1:** Schedule of data collection

	**At identification**	**At recruitment**	**6-months**	**12-months**
Age, gender, language spoken	X	X		
Demographic information		X		
Index of Comorbidity		X		
Number medication classes		X	X*	X
St George's Resp Ques		X	X	X
Spirometry		X	X	X
Immunisation status		X	X	X
Patient knowledge of COPD		X	X	X
Patient satisfaction with care		X	X	X
Smoking status: self-report		X	X	X
CO analyser		X	X	X
Health status (SF12)		X	X	X
Health service use		X	X	X
Value of partnership		X	X	X
Role and value of care plan				X

* respiratory medications only

Qualitative data about the value of the nurse-GP partnership and the role of the care plan will be collected from the intervention group by structured interviews at the conclusion of the project following collection of the 12 month quantitative outcomes.

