### Quantitative outcome measures

**Patient quality of life: (hypothesis 1) **was assessed using the St George's Respiratory Questionnaire (SGRQ) [22] at baseline and 12 month follow up. The SGRQ is a self-administered instrument designed specifically for respiratory disease. It is a 50-item instrument from which are calculated a total score and three component scores: symptoms (distress caused by respiratory symptoms), activity (physical activities thai are limited by breathlessness) and impacts (social and psychological effects of the disease). The SGRQ is scored from zero to 100 where zero indicates best quality of life and 100 worst. A change in score of four is considered to be clinically significant [22,23].

**Lung function: (hypothesis 1) **Spirometric function was measured before and 10 minutes after the administration of 200 μg sulbutamol via large volume spacer, according to standard methods. Forced expiratory volume in one second (FEV_1_) and forced vital capacity (FVC) were recorded.

***Patient health status*: (hypothesis 1) **was measured using the SF-12 [24], a generic measure of health impairment. The SF-12 gives two scores, the mental components scale and the physical component scale, which both have a mean of 50 and a standard deviation of 10.

***Health service use*: (hypothesis 1) **the number and type of general practice, specialist, community health, and hospital services used during the 12 months study period were recorded using a patient checklist of services.

***Immunisation status*: (hypothesis 2) **details of immunisation status for influenza and pneumococcal infection were collected by patient report.

***Patient knowledge *(hypothesis 2) **of the steps that can be taken to reduce the progression of COPD was assessed using the same measure as in the previous trial [20]. Patients were asked to name up to three things that they could do to prevent progression of their lung disease.

***Patient satisfaction*: (hypothesis 2) **with the overall management will be measured at 12 months using the questionnaire used in our previous study [20]. In addition, focus groups will also be conducted with a sub-set of patients in the intervention group to explore the issues even further.

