#### Statistical Analysis

Data are stored in an Access database and will be exported for analysis to SPSS. Analysis will be by intention to treat. Intra-cluster (practice) correlation coefficients will be determined and published for all primary outcome variables to assist future research. Potential confounders will be compared between groups to confirm that the randomisation has provided the appropriate balance.

The effect of the intervention on outcomes measured on a continuous scale (such as SGRQ score) will be estimated and tested using mixed model analysis of variance in which time and treatment group will be fixed effects and GP practice and subject nested within practice will be random effects. The effect of the intervention on the dichotomous variables (such as smoking status, patient knowledge) will be analysed using generalised estimating equations with a logistic link and a model structure that is analogous to that described above.

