#### Sample size calculations

The primary outcome variable will be 'between group' differences in post-test (12-months) is mean SGRQ scores. Data from our previous study [20] demonstrates that the between subject standard deviation in SGRQ scores is 13. The recommended minimum detectable difference to use for sample size calculations with SGRQ is 4.0 [22,23]. We have based our calculations on a intra-cluster correlation coefficient of 0.01 and a resultant design effect of 1.09 for a cluster size of 10 [26]. With this design effect the study has a > 80% power to detect a difference of 4 or greater in SGRQ. This requires at least 20 practices in each group and at least 10 patients per practice and that is at least 200 subjects in each group, (calculations in PASS software).

We estimated that the prevalence of COPD among general practice patients would be about 4.0%, slightly higher than population estimates [3]. Assuming that there are 1,500 adult patients registered with each GP then we would expect that there would be 60 patients with COPD. If a third of these patients would be eligible and consent to participate in the study, thus we will recruit 20 patients per practice. Taking a conservative approach and assuming 10 patients consent per practice, then to achieve 400 patients we will need to recruit 40 GP practices. As previously stated there are currently 785 GPs in 467 practices in SWS. Based on our previous experience of EPC evaluation [14] where 71% of the GPs contacted took part in the research we expect to be able to recruit the numbers of GPs and practices needed for this efficacy trial.

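### The mixed model names only practice and patient as random effects, so a 12-month effect that uses baseline leaves out practice-level variation in change, and its interval is too narrow unless practice effects are perfectly stable

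*Protocol article*

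**What the plan says.** The Statistical Analysis section of the protocol article gives one model for continuous outcomes such as SGRQ, in which "time and treatment group will be fixed effects and GP practice and subject nested within practice will be random effects". The abstract repeats it: "GP practice and subject nested within practice will be random effects". Neither place names a practice-by-time effect, a random slope or a residual covariance structure, and no group-by-time term is listed.

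The section Outcome evaluation places measurements "at recruitment (baseline), 6 months and at 12 months after randomisation", and Table 1 marks SGRQ at all three visits. The section Quantitative outcome measures lists SGRQ only "at baseline and 12 month follow up".

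The section Sample size calculations states: "The primary outcome variable will be 'between group' differences in post-test (12-months) is mean SGRQ scores". It does not say how baseline enters that comparison. The Statistical Analysis section also promises to publish practice-level intra-cluster correlations for the primary outcomes.

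**The concern.** A constant practice intercept says that a practice's departure from the mean is the same at baseline, 6 and 12 months. It therefore subtracts out of any contrast that sets 12 months against baseline. The remaining error is within-patient variation, treated as if patients had been randomised one by one. But practices were randomised, and the intervention runs through a nurse-GP partnership inside each practice, so change is what could well differ between practices. If it does, the standard error is too small. The practice-level part of this error can go in one direction only.

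A second, separate effect acts at patient level. Constant intercepts make all pairs of visits equally correlated. If baseline and 12 months are less correlated than adjacent visits, the pooled residual is too small for the 12-month change.

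The fault lies in the error term. Adding a group-by-time term to the same random part does not remove it. At stake are the 5% level and the width of the interval for the main result, if that result uses baseline.

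**Working it through.** **Inputs from the article (Sample size calculations).** SD 13 ("the between subject standard deviation in SGRQ scores is 13"); difference 4 ("The recommended minimum detectable difference to use for sample size calculations with SGRQ is 4.0"); ICC 0.01; 10 patients per practice; 20 practices per arm.

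**Assumptions, not in the article.** Two-sided 5% test; within-patient correlation between visits ρ = 0.5 to 0.8; correlation of practice effects between visits (CAC) of 1, 0.8, 0.5 or 0.

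**Step 1: the plan's own figure.** Design effect = 1 + 9 × 0.01 = 1.09. SE of the 12-month difference = 13 × √(2 × 1.09/200) = 1.357. Power = Φ(4/1.357 − 1.96) = Φ(0.987) = 83.8%, or 81.9% with a t test on 38 df. The stated power above 80% reproduces. It refers to the plain 12-month difference.

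**Step 2: change contrast under intercepts only.** As shares of total variance, let v_pt = ICC × (1 − CAC), v_e = (1 − ICC)(1 − ρ) and m = 10.

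- True variance of a practice-mean change: 2σ²(v_pt + v_e/m).
- Variance the model uses: about 2σ²(v_e + v_pt)/m.
- R = (v_pt + v_e/m) / [(v_e + v_pt)/m]; false positive rate = P(|Z| > 1.96/√R).

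Worked case, ICC 0.01, CAC 0.5, ρ 0.7: v_pt = 0.005 and v_e = 0.99 × 0.3 = 0.297. R = 0.0347/0.0302 = 1.149, √R = 1.072, rate 6.7%. In SGRQ points, the true SE is √(2 × 2 × 169 × 0.0347/20) = 1.08, while the model reports √(2 × 2 × 169 × 0.0302/20) = 1.01.

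| CAC (ICC 0.01) | √R, ρ = 0.5 | √R, ρ = 0.8 | False positive rate |
|---|---|---|---|
| 1 | 1.000 | 1.000 | 5.0% |
| 0.8 | 1.018 | 1.044 | 5.4-6.0% |
| 0.5 | 1.044 | 1.105 | 6.0-7.6% |
| 0 | 1.085 | 1.197 | 7.1-10.2% |

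Simulated trials with no effect (40 practices × 10 patients × 3 visits, 8,000 per setting) agreed with the formula. A t test on practice-mean changes with 38 df gave 4.6-5.6% in every setting. The plain 12-month difference gave 4.5-5.5% at ICC 0.01.

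**Step 3: decaying patient correlation, stable practice effects.** Take correlations of 0.75 for adjacent visits and 0.65 for baseline with 12 months. The pooled residual is proportional to 1 − (0.75 + 0.75 + 0.65)/3 = 0.283, but the change needs 1 − 0.65 = 0.35. R = 0.35/0.283 = 1.24, √R = 1.11, rate about 7.8% (simulated 8.2%). This needs three SGRQ visits. With only baseline and 12 months there is one correlation and the effect vanishes.

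**Step 4: the ICC.** If it were taken from the pooled three-visit model, the practice variance share at ICC 0.01 and CAC 0.5 would come out at about 0.005 + 0.005/3 = 0.0067, against 0.01 at the 12-month visit.

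**The case against.** The strongest reply is that the affected contrast is not the one the plan names. The primary outcome is a 12-month group difference, not a change, and only time and group are listed as fixed effects. The group effect in that literal model is a between-practice comparison, so practice variance does enter its error, and the plain 12-month difference also stays near 5%. This part stands: no text commits the trial to the affected contrast. But the literal group effect averages over the visits, baseline included, so it is not the 12-month effect either. Once a group-by-time term is added to obtain one, the article leaves open whether the result is read against baseline, and doing so is a usual reason for modelling the baseline visit.

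The second reply is that covariance structure and degrees of freedom belong in an analysis plan that is not shown. Silence on those details is indeed no fault. The random effects, however, are stated, twice and in the same terms, and constant intercepts are their plain reading.

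A reader might infer that the trial's false positive rate is 7-10% or more. The article does not support that without conditions. At its own ICC of 0.01, the practice-level mechanism spans that range only when practice effects are wholly uncorrelated between visits. Adding 1% practice-by-visit variance to a stable 1% gives 7.1-10.2%, but the 12-month ICC is then 0.02, twice the planned value. An ICC of 0.05 gives 7.2-10.4% at CAC 0.8 and 10.4-17.1% at CAC 0.5, but no such ICC appears in the article. The decay effect depends on three SGRQ visits, on which Table 1 and the text disagree. Nor does the article say that the published ICC will come from the pooled model.

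**Conclusion.** The point holds in conditional form. As written, the model leaves practice-level variation in change out of any 12-month effect that uses baseline, and the interval is then too narrow unless practice effects are perfectly stable. At ICC 0.01 the standard error should be about 2-4% larger at CAC 0.8, 4-11% at CAC 0.5 and 9-20% at CAC 0, with the false positive rates tabulated above. If SGRQ is taken three times and patient correlation decays, about 8% is possible even with stable practice effects. These figures are for the change contrast and rest on assumed correlations and a two-sided 5% level. They do not show that the plain 12-month comparison or its stated power is wrong. This is a cheap improvement to the analysis, not a defect that undermines the design.

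**What to change.** In the Statistical Analysis section, and to match in the abstract, state the primary analysis as a linear mixed model of 12-month SGRQ with baseline SGRQ as covariate and a random practice effect, with degrees of freedom based on the roughly 40 practices (Satterthwaite or Kenward-Roger). This delivers the stated 12-month comparison, uses the baseline collected and carries practice variance into the error.

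If the repeated-measures model is kept, add a practice-by-time random effect and an unstructured within-patient covariance, and say how baseline enters the 12-month contrast. Report the practice ICC for the 12-month outcome. Reconcile the SGRQ visits in Table 1 with the text.

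The cost is wording and, in the second option, a few more variance parameters; no new data are needed. The downside is a slightly wider interval than the intercept-only model would report, about 7% in the worked case (1.08 against 1.01).

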### Lesson learnt from a previous study

A randomised controlled trial (RCT) [20] conducted in 1998–99 which evaluated the effect of a brief, nurse-led intervention at 1 week and 4 weeks interval after discharge from hospital on clinical outcomes in patients with COPD. The aim was to evaluate the efficacy of limited community based care provided by nurses to COPD patients. Results from this study demonstrated limited success. There were some improvements in activity and knowledge scores of patients in the intervention group and they were more satisfied with their care, but there was no impact on rates of emergency department presentation and hospital readmission. We subsequently attributed the failure of the intervention to three key reasons 1) GPs were not sufficiently involved in the patient care (evident by the fact that only 31% of the GPs recalled having received patient related information (care plan) from the nurses), 2) there was no formal partnership between GPs and nurses streamlining patient care, and 3) the unavailability of universally accepted guidelines for management of COPD such as, COPDX.

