### Aim of the study

The aim of this study is to test a new approach to improving the care of patients with COPD managed in general practice. The intervention involves a registered nurse with specific training working in partnership with the patient, GPs and other health professionals to provide evidence-based care according to the Australian COPDX guidelines. The research aims to determine the impact of this partnership on the quality of care and health outcomes for patients with COPD at six and 12 months follow-up.

These are the hypotheses being tested:

1. That in patients with COPD, the intervention improves disease-related quality of life and overall health including patient health status, lung function and health service use.

2. That the intervention improves the quality of care provided to patients with COPD and that this will impact on knowledge, immunisation compliance, smoking cessation and satisfaction with care.

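### Patient knowledge is collected with an item allowing up to three answers but analysed as yes/no; if the answers are counted, a single cut gives up information on a hypothesis 2 outcome

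*Protocol article*

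**What the plan says.** **Collection.** Under Quantitative outcome measures, the knowledge item reads: "Patients were asked to name up to three things that they could do to prevent progression of their lung disease". Table 1 schedules it at recruitment, 6 months and 12 months. The same section says that the measure is the one used in the investigators' previous trial.

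**How that trial's results are described.** The section on lessons from the previous study reports: "There were some improvements in activity and knowledge scores of patients in the intervention group".

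**Analysis.** The Statistical Analysis section assigns the "dichotomous variables (such as smoking status, patient knowledge") to GEE with a logistic link. The Analysis paragraph of the abstract says the same. Continuous outcomes get a mixed model with time and treatment group as fixed effects, and with practice and subject within practice as random effects.

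**Role.** Knowledge belongs to hypothesis 2, which expects that improved quality of care "this will impact on knowledge, immunisation compliance, smoking cessation and satisfaction with care". It is not the primary outcome.

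The article prints no rule for turning up to three answers into a yes/no result, no expected distribution of answers, and no effect size or power for knowledge.

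**The concern.** An item that accepts up to three answers naturally gives a graded result, and the article's own word for the earlier results points the same way. The analysis nevertheless commits to two levels. If the answers are counted, a patient who moves from one valid action to two, or from two to three, contributes to the treatment effect only when that step crosses the cut.

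Knowledge is one of four outcomes named in hypothesis 2, and patient education is a listed component of the care plan. A real but graded improvement could therefore be missed or estimated less precisely, although the finer data have already been collected. The choice of a binary analysis is a stated method, so it can be judged from the article even though the exact threshold may be recorded elsewhere.

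**Working it through.** **1. The plan's own power figure.** The only one concerns the SGRQ. Inputs from Sample size calculations: SD 13, difference 4.0, 200 per group, ICC 0.01, cluster size 10. Two-sided 0.05 is assumed, since alpha is not stated.

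- Design effect = 1 + 9 × 0.01 = 1.09; effective n per group = 200 / 1.09 = 183.5.
- Standard error = √(2 × 13² / 183.5) = 1.357; 4 / 1.357 = 2.947; power = Φ(2.947 − 1.96) = 83.8%.
- With a t reference on 38 degrees of freedom (40 practices) it is 81.9%.

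Both agree with the stated figure of more than 80%. Nothing below alters it.

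**2. Information kept by a single cut of a 0–3 count.** Let p₀ to p₃ be the shares naming 0, 1, 2 and 3 valid actions, and q the share below the cut. Under proportional odds and for a small effect, the information in the binary outcome relative to the full ordinal count is

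3q(1 − q) / (1 − Σpᵢ³).

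The design effect is assumed equal for both analyses and cancels.

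Example, equal quarters: Σpᵢ³ = 4 × 0.25³ = 0.0625. For the cut at 2 or more, q = 0.5, so 3 × 0.25 / 0.9375 = 0.80, a 20% loss. For the cut at 1 or more, q = 0.25, so 3 × 0.1875 / 0.9375 = 0.60, a 40% loss.

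All shares in this table are assumptions:

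| Shares 0/1/2/3 (%) | Loss, cut ≥1 | Loss, cut ≥2 | Loss, cut 3 |
|---|---|---|---|
| 25/25/25/25 | 40% | 20% | 40% |
| 40/30/20/10 | 20% | 30% | 70% |
| 20/40/30/10 | 47% | 20% | 70% |
| 50/30/15/5 | 11% | 43% | 83% |
| 60/25/10/5 | 6% | 50% | 81% |
| 70/20/8/2 | 3% | 58% | 91% |

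**3. Wider range.** In 10,247 simulated distributions with every level above 5%, the best cut lost a median of 18%. The 5th to 95th percentiles were 6% to 30% and the extremes 1% and 42%; 87% lost less than 25%. Over all cuts the median loss was 31%.

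**4. Meaning for power.** If the ordinal analysis had 80% power, the binary analysis would have Φ((1.96 + 0.842) × √(1 − loss) − 1.96). That is 76% at a 10% loss, 71% at 20%, 65% at 30%, 58% at 40% and 43% at 60%.

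**5. Illustration at the planned size.** Assume a common odds ratio of 1.7 (not in the documents) and N = 400 / 1.09 = 367. Ordinal information is V = (N/12)(1 − Σp̄ᵢ³) and binary information is (N/4)q̄(1 − q̄), where bars are averages over the two arms. Power is Φ(ln 1.7 × √V − 1.96).

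With control shares 25/35/25/15, ordinal V = 28.4 and power is 81%; the cut at 2 or more gives V = 22.8 and power 72%, an efficiency of 0.80. With control shares 40/30/20/10 and 10/30/35/25, ordinal power is 80%. The best cut then gives 68% and 67% (losses of 25% and 26%), and the worst gives 40% and 28%.

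**6. Comparison with mean scores.** Replacing the ordinal analysis by a comparison of mean 0–3 scores gives similar losses in most rows of the table. In the two most skewed rows, however, the cut at 1 or more is slightly more efficient than the mean (by 3% and 8%). The statement that every cut loses information therefore refers to the ordinal analysis.

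**The case against.** The strongest reply is that the 0–3 score is not in the document. The item asks for up to three things; it does not say that answers are summed or marked valid. They could be coded as a particular action named or not named, or as any valid answer against none. The measure comes from the previous trial, whose scoring is not shown, and an article may leave such a rule to the full protocol or analysis plan. This stands, so the efficiency argument is conditional on a count.

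For the same reason, a reader might infer that the threshold is open and could be picked after the data are seen. The documents do not support that: the threshold may already be fixed in a source not shown.

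A reader might also infer that the binary analysis discards at least a quarter of the information. That is not a floor. The documents give no distribution, cut or effect size for knowledge, and a well-placed cut often loses less.

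Finally, a binary outcome can be a deliberate choice, if the question is whether a patient knows enough. Logistic GEE is a valid clustered analysis of such an outcome, and no bias is at issue. That stands too, but the article gives no such reason, and its own description of earlier results as scores points to a graded measure.

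**Conclusion.** The point holds as a minor one. The article collects knowledge with an item that allows a graded answer, describes earlier results as scores, and commits to a two-level analysis.

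If the answers are counted and proportional odds is a fair description, the best-placed cut loses about 3% to 30% of the information. The ten named distributions examined in the relative-information check, six of them tabulated, give 3% to 22%; the odds-ratio scenarios give 20% to 26%; the simulated 95th percentile is 30%. Poor cuts lose far more, up to about 90% in the most skewed examples. These sizes rest on assumed distributions and on a common design effect.

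A reader might take this as a threat to the trial's main conclusion. It is not: the primary outcome is SGRQ at 12 months, the sample size rests on it alone, and no power is claimed for knowledge.

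**What to change.** Make the number of valid actions named (0–3) the main knowledge outcome, and state in advance what counts as valid. Analyse it with an ordinal model, or with the mixed model already planned for continuous outcomes, with practice as a random effect and the baseline score taken into account. The ordinal model is the safer choice if most patients name nothing. Report the proportion reaching one prespecified threshold as a descriptive summary only. If the measure is in fact coded by a specific action named or not named, print that rule instead.

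The cost is a change of analysis wording. No new data are needed, since Table 1 already schedules the item at all three visits, and by the article's time plan the follow-up visits were still to come. The downside is a proportional-odds assumption (or equal spacing, for the mixed model) to check, and an effect measure slightly harder to explain than a difference between two proportions.
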